### Allocation

After completing the screening questionnaire, participants will be randomized in the intervention group or in the waiting-list control group in which participants receive care as usual, with an allocation ratio of 1:1. Randomization will be performed by one author ([name]) using Castor (https://www.castoredc.com). The OPs, PGAP coaches, and participants will not be blind to the condition of the participants. After randomization, all participants are labeled with a research code consisting a unique number in order to stay anonymous.

### Intervention

PGAP consists of a maximum of 10 weekly one-to-one sessions of a trained PGAP coach with a worker [13]. PGAP can be provided face-to-face, online, or by telephone [13, 25]. For this study, all sessions will be provided online through Zoom. The sessions have a duration of one hour. During the sessions, the PGAP coach uses different techniques to reduce limiting cognitions and perceptions in order to stimulate (work) participation. Participants are encouraged to talk about the difficulties they experience as a result of their health complaints and learn to be more aware of their thoughts in challenging situations and how to react in challenging situations. In addition, they learn about the importance of staying active, planning activities, and setting goals and are encouraged to resume discontinued activities. An introduction video is used to inform the worker about the procedures and objectives of the PGAP intervention. All workers will be given a workbook with information about the importance of sleep, social activities, and exercise, in which also activities can be scheduled. The workbook is also used to guide participants through exercises aimed at for example reducing catastrophizing thoughts and perceived injustice. The workbook will be translated in Dutch and the introduction videos will be subtitled in Dutch. A professional translation service, a worker with chronic health problems, the developers of PGAP, and the authors of this article will all be involved in the translation of the PGAP materials from English into Dutch. The content of the 10 sessions of PGAP is summarized in Table 2.

**Table 2 Tab2:** Content PGAP sessions [13]

Session	Content
Session 1	– Use of disclosure to establish a therapeutic relationship – Discussing activities that were performed by the client before the start of his/her complaints – Instructions on how to use the client workbook
Session 2	– Introduction to activity planning – Re-establishing pre-injury activity structure – Introduction to walking routine
Session 3	– Setting short and long-term activity goals – Planning activity involvement in relation to goals
Session 4	– Techniques targeting disability beliefs – Mid-treatment evaluation to see whether return to work is possible
Session 5	– Feedback about the mid-treatment evaluation – Introduction to thought monitoring to target catastrophic thinking
Session 6	– Exposure techniques to facilitate re-engagement in previously avoided activities
Session 7	– Continued application of techniques introduced in sessions 5 and 6
Session 8	– Applying task decomposition techniques to feared activities of the workplace
Session 9	– Problem-solving challenges to resumption of occupational activities – Final evaluation
Session 10	– Evaluation feedback and discharge planning

From “A Psychosocial Risk-Targeted Intervention to Reduce Work Disability: Development, Evolution, and Implementation Challenges” by M.J.L. Sullivan, H. Adams, and T. Ellis, 2013, *Psychological Injury and Law, 6,* 253

The main goal of PGAP is to decrease limiting cognitions and perceptions and to increase work participation. PGAP finishes if the worker has returned to work. Therefore, it is possible that workers do not need all 10 sessions. After the fourth session, the worker completes an evaluation questionnaire to see whether limiting cognitions and perceptions are decreased. The PGAP coach and worker discuss, with the input of the scores on the evaluation questionnaire, whether RTW is possible. If limiting cognitions and perceptions are decreased and RTW is possible, the fifth session of PGAP is the last session for the participant. If RTW is not possible, the participants will continue the PGAP sessions until RTW is possible. The PGAP intervention will be provided by OH practitioners after completing a training to become a PGAP coach. The training consists of watching 9 webinars, participating in a 2-day training workshop to acquire the skills necessary to deliver PGAP, and passing a final exam.

During the trial, meetings will be scheduled between the PGAP coaches and an experienced PGAP supervisor in which PGAP coaches can discuss the progress of their cases or any problems they might experience during the trial. To obtain information about the compliance of the PGAP coaches to the PGAP protocol, all PGAP coaches will complete a short checklist after each session. In this checklist, the PGAP coaches can indicate if important goals per session are met and which topics during the sessions were discussed.

The participants in the control group will receive care as usual, which could differ between the participants depending on their health issues and duration of sick leave. After the participants in the control group complete the final assessment, they will have the opportunity to participate in PGAP. The participants in both the intervention and control groups are allowed to participate in other interventions or care during the trial. Whether they participate in other types of care will be assessed in the questionnaires.

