**Methods:**

This study is a randomized controlled superiority trial with two (parallel) groups, in which workers on sick leave are randomly assigned to an intervention group (PGAP intervention) or to a waiting-list control group (care as usual). The PGAP intervention consists of a maximum of 10 weekly individual sessions provided by a trained PGAP professional in which the worker learns about staying active, planning activities, and setting goals. Participants in this risk-targeted behavioral activation intervention also learn to be more aware of their cognitions and perceptions and learn about solution-focused problem-solving skills in challenging situations. The primary outcome is the degree of catastrophizing. Secondary outcomes are other personal cognitions and perceptions (e.g., expectations regarding return to work, self-efficacy), health symptoms (e.g., fatigue, depression), work participation (e.g., sick leave status, work hours), and other work-related outcomes (e.g., workability, quality of working life).

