Because the empirically supported effects of PGAP are positive, it is aimed at a broad group of patients and it can be provided by different OH professionals, PGAP is a promising intervention to change cognitions and perceptions and improve work participation. However, it is unknown whether PGAP is effective in the Dutch context in changing cognitions and perceptions and stimulating work participation. Because occupational healthcare differs across countries, it may be possible that the effect of PGAP in comparison to care as usual in the Netherlands differs from other countries that studied the effects of PGAP [21]. Besides, although different studies demonstrate positive effects of PGAP, the effects of PGAP are not studied among workers with different chronic health problems in a randomized controlled trial yet. Therefore the objective of this protocol article is to describe the design of a randomized controlled superiority trial with two parallel groups to study whether PGAP (1) is effective in decreasing limiting cognitions and perceptions and (2) is effective in increasing workability and work participation of workers with chronic health problems in the Netherlands. We hypothesize that participants who participate in PGAP score lower on limiting cognitions and perceptions, such as catastrophizing, fear-avoidance, perceived injustice, and perceived disability than participants who do not participate in PGAP. We also hypothesize that participants who participate in PGAP score higher in work ability, have a higher chance to RTW and have more working hours than participants who do not participate in PGAP.

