### Study setting

This project was initiated by the Department of Public and Occupational Health, Coronel Institute of Occupational Health of the Amsterdam UMC location University of Amsterdam, which is located in the Netherlands. The Netherlands has about 17,4 million inhabitants. The participants will be recruited by OPs and OH practitioners from a national occupational health service (OHS), which has multiple branches spread over the Netherlands. The core business of the OHS is to offer services to different organizations with the goal to increase the health of workers, promote sustainable employability, prevent sick leave, and offer support for RTW after sick leave. The task of the OP in the Netherlands is to prevent work-related diseases and to support workability and RTW after sick leave. The OH practitioner collaborates with the OP and works in task delegation of the OP to reduce the work pressure of the OP. Both OPs and OH practitioners have consultations with workers to promote workplace health, to prevent sick leave, or to support RTW. Six OH practitioners from the OHS will also be the PGAP providers (“coaches”) in this study. The six OH practitioners were selected by the director of the OHS (HZ) by convenience sampling. The OH practitioners were eligible to become a PGAP coach if they could understand and speak Dutch and English.

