### Participants

Persons are eligible for inclusion if they are workers between 18 and 65 years old. To participate, persons have to be on sick leave for at least 3 weeks or have frequent spells of sick leave, defined as 3 or more times a year. Eligible participants need to be able to speak, read and write in Dutch and need to be in paid employment. They are eligible if they experience functional limitations associated with their mental or physical health problems. In addition, they need to have at least one cognition or perception that can limit work participation; catastrophizing thoughts, perceived injustice, fear-avoidance beliefs, or disability beliefs. Whether the workers have these limiting cognitions and perceptions will be indicated by a score above the threshold on different questionnaires which are described in the outcome measures section of this protocol.

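### Frequent-spell entrants may be at work at T0, so the binary work-status outcome can count staying at work as a return and does not cleanly test the return-to-work hypothesis

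*Protocol article*

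**What the plan says.** **Who may enter.** The Participants section gives two routes joined by an *or*: at least 3 weeks of sick leave, or to "have frequent spells of sick leave, defined as 3 or more times a year". The Recruitment procedure repeats the pair as long-term or frequent sick leave. Neither section requires a frequent-spell worker to be absent at screening. According to the Study setting, the recruiting professionals "have consultations with workers to promote workplace health, to prevent sick leave, or to support RTW", so they also meet people who are working. The abstract is narrower: "workers on sick leave are randomly assigned to an intervention group".

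**What is hypothesized.** The Background expects that PGAP participants "have a higher chance to RTW and have more working hours than participants who do not participate in PGAP".

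**How work status is analysed.** The Statistical analyses section specifies a mixed effects logistic regression at T1, T2 and T3 on a two-category variable: back at work, or on sick leave. Baseline adjustment is stated for the SCS and, in the paragraph before the logistic model, for the continuous secondary outcomes. It is not stated for work status.

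**When PGAP ends.** The Intervention section says "PGAP finishes if the worker has returned to work". After the session 4 evaluation it says "If limiting cognitions and perceptions are decreased and RTW is possible, the fifth session of PGAP is the last session for the participant", and also "If RTW is not possible, the participants will continue the PGAP sessions until RTW is possible". The programme is capped at 10 sessions.

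**The concern.** The outcome label and the hypothesis presuppose that everyone is absent at T0; the eligibility criteria do not. A frequent-spell worker who is at work at screening and remains so falls in the back-at-work category at every follow-up, in either arm, although there was no absence to return from. The return-to-work effect is then averaged over people who could return and people who could not.

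Work participation is one of the trial's two stated aims, and a higher chance of return is an explicit hypothesis. A result on this variable would probably be reported as an effect on return to work, when part of it could be an effect, or no effect, on staying at work.

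The finishing rule has a smaller gap of the same kind: it is phrased around a return that a worker already at work does not have to make.

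**Working it through.** **1. The texts side by side, for a frequent-spell worker at work at T0**

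| Text | What it gives |
|---|---|
| Participants, Recruitment procedure | Eligible |
| Statistical analyses, work status | Counted as back at work at T1 to T3 if nothing changes |
| Background, return hypothesis | Not defined, because there is no return to make |
| Intervention, session 5 rule | Return is already possible, so the decision rests on whether cognitions have decreased |
| Intervention, continuation rule | Worded only for workers whose return is not yet possible, so silent if this worker's cognitions have not decreased |
| Secondary outcomes, readiness and motivation items | Separate items for people at work |
| Statistical analyses, hours and days worked | Adjusted for baseline |

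The mismatch is therefore confined to the binary outcome and, in a minor way, to the finishing rule.

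**2. The plan's own figure.** With a difference of 2.4, SD 3.0, two-sided 5% (sidedness assumed) and 80% power, the normal approximation gives 25 per group. Dropout of 15% gives 25/0.85 = 29.4, so 30 per group and 60 in total. The plan's sample size reproduces. It concerns the SCS and is not touched by this point.

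**3. Dilution (assumed inputs).** The documents give no split between the routes and no return rates. Let *f* be the share at work at T0, with equal stay rates in both arms. The observed difference is then (1 − *f*) × the difference among absent workers. For an assumed 30 points:

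- *f* = 0.10 (6 of 60): 27 points
- *f* = 0.20 (12 of 60): 24 points
- *f* = 0.30 (18 of 60): 21 points
- *f* = 0: 30 points, no effect

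**4. Chance imbalance.** When K at-work entrants are split at random over 30 and 30 (hypergeometric), the arms differ by 4 or more with probability 0.195, 0.333 and 0.399 for K = 6, 12 and 18. If 90% stay at work and 40% return in both arms, a difference of 4 moves the comparison by (4/30) × (0.90 − 0.40) = 0.067. The standard error at an overall share of 0.45 is √(2 × 0.45 × 0.55/30) = 0.128. The shift is about half a standard error and is already part of it.

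**5. Which analysis is most sensitive?** This step uses 40,000 simulated trials of 30 per arm, with assumed return of 40% (control) and 70% (PGAP) among absent workers. Entries are the mean risk difference divided by its standard deviation, for K = 6 / 12 / 18. *Adjusted* is the Mantel–Haenszel risk difference stratified by T0 status.

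| Assumed stay rate, control v PGAP | All 60, unadjusted | Absent at T0 only | All 60, adjusted |
|---|---|---|---|
| 90% v 90% | 2.23 / 2.00 / 1.77 | 2.33 / 2.19 / 2.05 | 2.29 / 2.09 / 1.89 |
| 75% v 90% | 2.35 / 2.22 / 2.14 | 2.33 / 2.18 / 2.04 | 2.37 / 2.28 / 2.20 |

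Restriction to absent workers is more sensitive than the unadjusted comparison only when PGAP has little effect on staying at work. Adjustment for T0 status gives a small gain over the unadjusted comparison in both settings.

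**The case against.** The strongest defence has four parts.

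- **Covariates and subsets belong in the analysis plan.** The article says one exists, and it is not shown. This stands as far as it goes: a missing T0 term would not by itself be a finding. What remains is the printed outcome label and hypothesis, which do not fit the printed eligibility.
- **The label is loose wording for not being on sick leave.** That status is meaningful for frequent-spell workers, who can relapse. This stands, and it is the reason to keep all randomized workers in the model. It does not turn that analysis into a test of return.
- **Other outcomes cope.** The readiness and motivation items branch by work status, and working hours and days are adjusted for baseline. This stands and limits the point to one binary secondary outcome.
- **The abstract is shorthand.** Agreed; the Participants section governs.

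Three stronger readings are tempting, and the documents do not support them. A reader might infer that the work-status comparison is *biased*. It is not: it compares everyone as randomized, and chance imbalance is already in its standard error. A reader might infer that such workers would get *no sessions*, since the finishing condition is met before session 1. That is strained: they are recruited for functional limitations and limiting cognitions and allocated to receive PGAP, and the two-condition session 5 rule with the 10-session cap largely covers them. A reader might also infer that restricting to absent workers *costs no sensitivity*. The second row of the table shows that it can.

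**Conclusion.** The point holds in a limited form. The trial admits workers who may be at work at T0, and its binary outcome would count those who never left as returns. As printed, the analysis compares being at work with being on sick leave; it does not cleanly test the hypothesis of a higher chance of return.

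The size is unknown and may be nil, because the number at work at T0 is not given. The reduction from 30 to between 27 and 21 points rests on an assumed 10% to 30% at work at T0, an assumed 30-point difference among absent workers, and equal stay rates. The primary SCS comparison and the sample size are unaffected. This is a cheap improvement to a secondary analysis, with a minor clarification of the finishing rule.

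**What to change.** **Statistical analyses**

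1. Label the binary outcome as at work or on sick leave.
2. Keep all randomized workers in the mixed logistic model and add T0 sick-leave status as a covariate.
3. Test the return-to-work hypothesis in participants on sick leave at T0. Because "After completing the screening questionnaire, participants will be randomized in the intervention group", and that questionnaire is the T0 measurement, the subset is fixed before allocation and the comparison within it is still randomized.

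**Intervention**

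Add one sentence: for workers at work at T0, the session 5 decision rests on whether limiting cognitions and perceptions have decreased; otherwise sessions continue, up to 10. Leave the rule for absent workers, "If RTW is not possible, the participants will continue the PGAP sessions until RTW is possible", as it stands.

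**Cost**

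This takes a few sentences, submitted to the ethics committee by the amendment route under Data monitoring, ideally before the September 2022 start of recruitment. Sick-leave status is already among the questions; it has to be in the T0 questionnaire. No participants or scales are added. The downside is that the return analysis uses fewer workers (54, 48 or 42 of 60 if 6, 12 or 18 are at work at T0), and it is more sensitive than the comparison of all randomized workers only if PGAP has little effect on staying at work.

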### Outcome measures

#### Primary outcomes

The primary outcome is catastrophizing thoughts as measured with the Dutch SCS [23]. The Dutch SCS is a modified version of the Dutch Pain Catastrophizing Scale [26] in which items are modified to make them better suited for individuals who do and who do not experience pain, but other mental or physical health problems. The questionnaire has 7 items with a three-point scale from “never” to “often.” The final score on the SCS can range from 0 to 14, in which a higher score indicates having more catastrophizing thoughts. Previous studies showed that the SCS is a reliable (Cronbach’s alpha .81–.89) and valid questionnaire to measure catastrophizing thoughts [23].

#### Secondary outcomes

Secondary outcomes are other cognitions and perceptions than catastrophizing, health symptoms, and different work-related outcomes.

Fear-avoidance beliefs will be measured with 5 items from the Dutch version of the Tampa Scale for Kinesiophobia (TSK) [27, 28]. The five items can be answered on a three-point scale from “do not agree” to “completely agree.” The final score can range from 0 to 10 in which a higher score indicates more fear avoidance. The Cronbach’s alpha of the Dutch TSK was .77 in previous studies [27].

Perceived injustice will be measured using a modified version on the Dutch Injustice Experience Questionnaire (IEQ) [29, 30]. The modified IEQ contains 5 items that can be answered on a three-point scale from “never” to “often.” The final score can range from 0 to 10 in which a higher score indicates more perceived injustice. Previous studies showed that the IEQ is valid and reliable (Cronbach’s alpha .92) for measuring perceived injustice [29, 30].

Perceived Disability will be measured using the Dutch version of the General Perceived Disability Index (GPDI), which is a modified version of the reliable (Cronbach’s alpha .86) and valid Pain Disability Index [31–33]. In the GPDI the wording of the items is modified to refer to symptoms of the conditions, instead of referring only to pain. The questionnaire contains 5 items that can be answered on an eleven-point scale from “no disability” to “total disability.” The final score can range from 0 to 50 in which a higher score indicates more perceived disability.

Self-efficacy in RTW will be measured using the Dutch version of the RTW Self-Efficacy (RTW-SE) Scale [34]. This questionnaire has 11 items with a six-point scale from “totally disagree” to “totally agree.” The RTW-SE score is computed by taking the mean score over the 11 items, in which a higher score indicates more self-efficacy in RTW. Previous studies indicated that the RTW-SE is a reliable (Cronbach’s alpha .90–.96) and valid measure for self-efficacy in RTW [34].

Quality of working life will be measured using the Dutch version of the valid and reliable (Cronbach’s alpha .91) Quality of Working Life Questionnaire (QWLQ) [35]. This questionnaire has 23 items with a six-point scale from “totally disagree” to “totally agree.” The overall QWQL score is calculated with a standardized score ranging from 0 to 100. A higher score indicates better quality of working life.

Workability will be measured using the Dutch version of the Work Ability Score and two additional questions of the reliable and valid Work Ability Index (WAI) [36–38]. The Work Ability Score is the worker’s self-assessment of his/her current ability ranging van 0 to 10. In the other two questions of the Work Ability Index, the workers rate his/her workability in relation to the physical and mental work demands. The questions can be answered on a five-point scale from “very poor” to “very good.”

RTW expectations will be measured using the questions: “What are your chances of being fully able to work one month from now?” and “What are your chances of being fully able to work three months from now?” The questions can be answered on a scale from 0 to 100%.

Readiness for RTW will be measured with the Dutch Readiness for RTW scale (RRTW) [39, 40]. This questionnaire has 21 items with a five-point scale from “strongly disagree” to “strongly agree.” Twelve of these items are only completed by participants who did not RTW and 9 items are only completed by participants who returned to work. The scores of this questionnaire indicate in which stage the worker is when it comes to returning to work: pre-contemplation, contemplation, preparation for action-self-evaluative, preparation for action-behavior, uncertain maintenance, and proactive maintenance. The Cronbach’s alpha for these dimensions varied from .65 to .82 in previous studies [39].

Motivation will be asked with one statement that can be answered on a five-point scale from “totally disagree” to “totally agree.” The statement for participants who returned to work is “I am motivated to stay at work.” The statement for participants who did not RTW is “I am motivated to RTW”.

Depressive symptoms will be measured with the Dutch version of the Brief Patient Health Questionnaire-9 (PHQ-9) [41]. The questionnaire contains 9 items which can be answered on a four-point scale from “not at all” to “nearly every day”. In addition, there is a tenth item in which the participant can indicate how difficult the problems of the participant have been lately. The final score can range from 0 to 27 in which a higher score indicates more severe depressive symptoms. The Cronbach’s alpha for the PHQ-9 varied from .86 to .89 in previous studies and was proven to be a valid questionnaire for measuring depressive symptoms [41].

Fatigue will be measured with the Dutch version of the Multidimensional Fatigue Inventory (MFI) [42]. The questionnaire contains 20 items which can be answered on a five-point scale from “yes, that is true” to “no, that is not true.” The final score can range from 20 to 100 in which a higher score corresponds with higher levels of fatigue. The MFI is a valid and reliable questionnaire for measuring fatigue (Cronbach’s alpha .84) [42].

Health-related quality of life will be measured using the Dutch version of the valid and reliable (test-retest correlation .76–.89) 12-item Short-Form Health Survey (SF-12) [43, 44]. The questionnaire contains 12 items related to physical and mental health. The final score can range from 0 to 100 in which a higher score corresponds with a better physical and mental health functioning.

Work participation will be measured by asking the participants about their current contract hours, about the mean days and hours they currently work during a week, and by asking them whether they have modified work. In addition, we ask the participants about their sick leave status.

To check the readability and face validity of the questionnaires, a worker with chronic health problems completed all the questionnaires and was asked for feedback.

